## Abstract

**Background:**

Many of the approximately 15 million people with a migration background living in Germany (19% of the population) are inadequately reached by existing healthcare provision. In the literature, the necessity for cultural adaptation of information material for patients with a migration background is often cited as a measure for improving healthcare.

In this study, culturally sensitive information material will be developed and evaluated for patients with a migration background and depression or chronic low back pain. In this respect, it will be examined whether culturally sensitive information material is judged as more useful by the patients than standard translated patient information without cultural adaptation.

**Methods/Design:**

The implementation and evaluation of culturally sensitive patient information material will occur in the framework of a double-blind randomized controlled parallel-group study in four study centres in Germany. Primary care patients with a Turkish, Polish, Russian or Italian migration background with a diagnosis of depressive disorder or chronic low back pain will be included and randomly allocated to the intervention group or the control group. In the intervention group, culturally sensitive patient information will be handed to the patient at the end of the physician consultation, while in the control group, standard translated patient information material will be provided. The patients will be surveyed by means of questionnaires following the consultation as well as after 8 weeks and 6 months. In addition to the primary outcome (subjective usefulness), several patient- and physician-rated secondary outcomes will be considered.

**Discussion:**

The study will provide an empirical answer to the question of whether persons with a migration background perceive culturally sensitive patient information material as more useful than translated information material without cultural adaptation.

**Trial registration:**

Deutsches Register Klinischer Studien (DRKS-ID) DRKS00004241 and Universal Trial Number (UTN) U1111-1135-8043.

## Background

A person’s healthcare is influenced by cultural and ethical values and attitudes as well as his or her migration experiences [1-3]. Language difficulties, a lack of information on the host country’s healthcare system and healthcare provision, deviating cultural beliefs, and a feeling of being misunderstood are central problems in the healthcare of persons with a migration background [4,5]. These barriers may be of elevated importance in chronic and multifactorially determined diseases, in which lifestyle changes are required for an enduring treatment success, for example, depression or chronic low back pain. To ensure successful changes in lifestyle, patients have to be adequately informed. An efficient way to inform patients is provided by written patient information material (for example, brochures), which increases knowledge about the illness and its treatment and is therefore a notable supplement to the consultation [6]. Patient information material can help the patient to develop a realistic perception of the course of the disease and increase his or her involvement [7]. It supports patients by informing them about sensible self-help activities and advising how to improve coping strategies [8]. Moreover, it helps patients to become aware of their own preferences when different treatment options are given and to make informed decisions.

When addressing patients with a migration background, merely translating patient information material into the patient’s mother tongue might not be sufficient to deal with cultural barriers. The understanding of the concepts of ‘health’ and ‘disease’ depends on the sociocultural context of a country, and therefore culturally sensitive information material that is designed to meet the unique needs of migrants has been called for [9]. Such material might help to improve the healthcare of persons with a migration background, by reducing cultural barriers and facilitating effective communication to help them to recognise and cope actively with diseases [9,10]. However, research on the effects of culturally sensitive patient information material is insufficient. To date, high-quality investigations focusing on the specific effect of culturally sensitive material compared with high-quality standard translations using a double-blind, randomized controlled multicentre design are lacking.

### Objectives

The aim of our study is to evaluate the effects of the provision of culturally sensitive information material to primary care patients with a migration background with depression or chronic low back pain in comparison with that of non-culturally adapted material. This will be assessed with regard to perceived usefulness of the material as judged by the patient (primary outcome) and other short- and medium-term cognitive, behavioural, clinical and healthcare-related outcomes.

## Methods/Design

The effects of a culturally sensitive version of written patient information material compared with a standard translated version will be evaluated in a double-blind, randomized controlled multicentre trial involving four study centres. Participating study centres are the Research Group on Psychotherapy and Health Services Research, Department of Psychiatry and Psychotherapy, Medical Center - University of Freiburg (primary study centre); the Department of Medical Psychology, University Medical Center Hamburg-Eppendorf; the German Foundation Against Depression (Stiftung Deutsche Depressionshilfe); and the Network of Physicians Oberhausen-Mülheim-Duisburg (Ärzte Netzverbund Oberhausen-Mülheim-Duisburg). The study was approved by the institutional review board of the University Medical Center Freiburg (number 375/10) and the local review boards responsible for local physicians (Ärztekammer Nordrhein, number 2012400; Sächsische Landesärztekammer, number EK-BR-74/12-1; Landesärztekammer Baden-Württemberg, number B-F-2012-065, and Ärztekammer Hamburg, number MC-307/12).

We chose depressive disorders and low back pain as medical indications as both conditions are among the leading causes of burden of disease worldwide [11]. Both conditions are often chronic, require an active involvement of patients in their own healthcare and are expected to be sensitive to cultural background. In addition, they are highly prevalent in German primary care [12,13].

To further increase generalizability, we chose to include patients with various migration backgrounds. Persons with a Turkish origin were included, as they constitute the largest group of migrants in Germany. Polish migrants are the group with the highest percentage of recent immigrants and the third largest group in total. Russian migrants are often late re-settlers with a German origin. Italian migrants are the largest group of European Union migrants and are among the traditional migrant workers in Germany.

The majority of patients are treated in primary care. Moreover, patient information plays a central role in primary care because it often serves as the source of first contact. General practitioners therefore have to provide initial information about illness and corresponding treatment options. Given the high numbers of patients treated in primary care and the central role of information material in this setting, we chose primary care as the setting for our study.

### Inclusion criteria

General practitioners will consecutively assess patients for eligibility. Adult primary care patients with a Turkish, Polish, Russian or Italian migration background and with unipolar depressive disorder or non-specific chronic low back pain will be included. Having a migration background is defined as being of non-German nationality, having a first language other than German, being born in another country, or having a parent who was born in a country other than Germany. To be included, patients have to report that they perceive their non-German origin as part of their identity. Unipolar depressive disorder is defined according to the International Classification of Disease, 10th revision (ICD-10: codes F32.xx, F33.xx, F34.1). In accordance with German national guidelines, chronic low back pain is defined as pain in the area beneath the costal arch, above the inferior gluteal folds, with or without referred leg pain, for more than 12 weeks and without signs of a specific cause (ICD-10 codes: M54.5, M54.8, M54.9). Potentially eligible patients will be identified using routine health records. Sociodemographic information will be confirmed within the consultation. Diagnosis will be based on clinical judgment.

### Exclusion criteria

To ensure a high external validity of our results, we have not formulated any exclusion criteria. However, owing to the type of intervention (written patient information material) and the response format (questionnaire), patients who are unable to read or respond to a questionnaire in the language of their respective migration background will not be eligible to participate in this study.

### Recruitment of general practitioners

General practitioners will be recruited by inviting academic training practices, practices of the cooperating networks and general practitioners (using public registers) to participate in the study. General practitioners will receive an allowance of €40.00 per patient recruited.

### Development of the interventions

In a first step, we will develop written patient information material for the indication of unipolar depression and chronic low back pain on the basis of current clinical practice guidelines (for depression, [12]; for chronic low back pain, [14]) in the German language. In addition to information on epidemiology, diagnostics and prognosis, treatment options and responsibilities of different healthcare providers will be explained using comprehensible language. The content of the developed patient information material will be discussed in an expert workshop with respect to accuracy and comprehensibility. To ensure the high quality of the material, we will include healthcare professionals (including at least one professional who was engaged in the development of the respective guideline) as well as patient representatives in the process. The final brochure comprises 12 pages and includes figures, pictures and illustrative case examples.

Second, the material will be translated by professional translators using the forward-backward translation procedure [15]. To this aim, the material will be translated by two independent translators. Based on the two versions, a third independent translator will develop a consensual version, and the consensual version will be translated back into German by a fourth independent translator. The original version and the back-translated version will be cross-checked by the third translator in cooperation with the research team. This process guarantees a high quality of the translated patient information material. The resulting material, termed the ‘standard translated version’, will be used as the control condition.

Third, cultural differences in the respective countries will be explored in order to develop the culturally sensitive version of the patient information material. The translated patient information material will be discussed with respect to its cultural appropriateness in four separate focus groups, one for each nationality. The focus groups will consist of four to ten people with a migration background. All focus groups will be conducted by the same moderators using a manual. The focus group sessions will be audio-recorded and transcribed. Two independent researchers will perform content analysis according to the methods of Mayring and Schreier [16,17]. Differences will be resolved by discussion with a third independent researcher. Based on these results, a culturally sensitive version of the patient information material will be developed. Cultural adaptations will primarily focus on presentation; the core information will remain unchanged.

Fourth, comprehensibility of the culturally sensitive version will be pilot-tested with two persons per migrant group. In this step, only definitely misleading or incomprehensible expressions will be modified. The resulting culturally sensitive version of the material will then be used in the intervention group.

### Administration

Patients will be recruited and informed of the study by the participating general practitioners within the consultation (-T_1_, enrolment, see Table 1). Informed consent will be sought from each participating patient. After informed consent has been provided, patients will receive a sealed envelope containing written patient information material in the form of a brochure and a questionnaire (T_0_, allocation). The contents of the envelopes (standard translated material versus culturally sensitive material) will be centrally randomized by means of a computer-based algorithm and stratified by physician, disease and migration background (Turkey, Poland, Russia, Italy) with varying block sizes, to ensure a balanced proportion of participants in the study conditions and to prevent predictability. Each physician, provided in advance with sets of envelopes, according to the disease and the migration background of the eligible patient, will simply hand the patient the next envelope from the appropriate group of envelopes. The envelopes will be prepared by the study centres, which will have no direct contact with patients. Blinding of general physicians and patients will be ensured through the use of sealed envelopes. Concomitant care will not be restricted in any way.

**Table 1 T1:** Study schedule

	**Study period**				
	**Enrolment**	**Allocation**	**Post-allocation**		**Close-out**
**Time point**	**-T**_ **1** _	**T**_ **0** _	**T**_ **1** _	**T**_ **2** _	**T**_ **3** _
**Enrolment**					
Eligibility screen	×				
Informed consent	×				
Allocation		×			
**Interventions**					
Culturally sensitive patient information material			×		
Standard translated patient information material			×		
**Assessments**					
**General practitioner rating**					
Diagnosis	×				
Treatment	×				
**Self-rating**					
Demographic information (age, sex, migration background, mother tongue, German language proficiency, education)*			×		
Acculturation (SMAS)			×		
Usefulness of information material (USE)			×	×	×
Knowledge of the disease*			×	×	×
Perceived cultural sensitivity*			×		
Behaviour change*				×	×
Illness perception (Brief-IPQ)			×	×	×
Symptom self-rating (PHQ-9, Core set)			×	×	×
Acceptance of the disease or treatment*			×	×	×
Adherence (MOS)				×	×
Satisfaction with physician (ZAPA)			×	×	×
Health care utilization*				×	×
Quality of life (WHO-5)			×	×	×

-T_1_, within the consultation; T_0_, after informed consent has been given; T_1_, after consultation; T_2_, 8 weeks; T_3_, 6 months; Brief-IPQ, Brief Illness Perception Questionnaire; MOS, Medical Outcomes Study (general adherence); PHQ-9, 9-item version of the Patient Health Questionnaire; SMAS, Stephenson Multigroup Acculturation Scale; USE, Usefulness Scale for Patient Information Material; WHO-5, WHO 5 Well-being Index; ZAPA, questionnaire assessing satisfaction with outpatient care, with a focus on patient participation; *, self-constructed items.

Patients in the intervention group will receive a culturally sensitive version and patients in the control group will receive a standard translated version of brochures. Patients will read the brochures after the end of the consultation, and will be asked to fill in the questionnaire and return it by post using a prepaid envelope (T_1_, after consultation). If patients do not respond, they will be reminded by phone (if possible) after 2 weeks and by post after 3 weeks. At 8 weeks (T_2_) and 6 months (T_3_) after the consultation, patients will be contacted by post and asked to fill in follow-up questionnaires. To ensure a sufficient response rate at each time point, patients will receive an unconditional reimbursement of €5.00, as this measure has been shown to be associated with an increased response rate [18].

### Primary outcome

The primary outcome will be the perceived usefulness of the written patient information material, as assessed by the patient using the Usefulness Scale for Patient Information Material (USE) following the consultation (T_1_). Patients will be blinded to their group assignment. This scale was developed in an independent inpatient population of 120 patients with depression or chronic low back pain. It is an instrument to measure the perceived usefulness of written patient information material from a patient’s point of view, and has nine items. The total score of the final version is a generic estimate, while the three subscales can be used to differentiate cognitive, emotional and behavioural aspects of usefulness. The USE has turned out to be a reliable and valid scale.

### Secondary outcomes

Perceived usefulness (USE) will additionally be assessed at T_2_ and T_3_, to investigate the perception of usefulness of the information material over time. Differences in the subscales will additionally be assessed. We will additionally assess the effects of the culturally sensitive material on knowledge of the disease (self-constructed items; at T_1_, T_2_, T_3_) and whether adapted patient information material is perceived as more culturally adequate (perceived cultural sensitivity; self-constructed items; T_1_). In addition, the level of implementation of behaviour promoted in the patient information material (behaviour change; self-constructed items; T_2_, T_3_), perception of disease (Brief Illness Perception Questionnaire, Brief-IPQ; T_1_, T_2_, T_3_[19]), symptoms of depression or back pain (Patient Health Questionnaire, PHQ-9, Core set; T_1_, T_2_, T_3_[20,21]), and acceptance of disease and the treatment (self-constructed items; T_1_, T_2_, T_3_) will be investigated. Finally, the effects of the culturally sensitive material on adherence (MOS general adherence items; T_2_, T_3_[22]), Satisfaction with the physician (ZAPA; T_1_, T_2_, T_3_[23]), healthcare utilization (self-constructed items; T_2_, T_3_) and quality of life (WHO 5 Well-being Index, WHO-5; T_1_, T_2_, T_3_[24]) will be assessed.

### Additional parameters

Data on the following demographic parameters will be collected via self-rating questionnaire: age, sex, migration background, mother tongue, German language proficiency and education. The acculturation of the patient will additionally be captured by means of a standardized instrument (Stephenson Multigroup Acculturation Scale, SMAS; T_1_[25]). Moreover, physicians will be asked about the patient’s diagnosis and treatment.

At the level of the general practitioner, we will assess general characteristics of the physician, such as age, sex, migration background, mother tongue and level of experience with other cultures via a self-rating questionnaire, to gain information on the generalizability of the results. At the level of the general practitioners’ practice, we will gather information on the number of practitioners in the practice, case load, consultations conducted in languages other than German, practice staff with a migration background, whether patient information material in languages other than German is already offered, and general practitioners’ estimated usefulness of patient information material for people with a migration background. Finally, we will assess the self-rated competence of the physician in dealing with persons with a migration background, the subjective need for education in dealing with persons with a migration background, the perceived impact of interaction problems and other barriers to treating persons with a migration background.

### Statistical analyses

The primary outcome (usefulness of written patient information material; USE) will be analyzed by a blinded statistician with a one-sided *t* test comparing the scores on the USE scale between the intervention and the control group. Secondary interval-scaled outcomes will be tested using *t* tests and analysis of covariance (ANCOVA, if baseline measurement of the outcome is available). In additional analyses, we will include acculturation (SMAS) as covariate and conduct subgroup analyses regarding disease, migration background, symptom severity and acculturation. The primary analysis will be performed according to the intention-to-treat principle, including all randomized participants. Missing data will be handled by applying linear mixed models and expectation-maximisation imputation. Secondary analyses will be performed in available cases.

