### Sample size

To be able to identify a small intervention effect (Cohen’s *d* of 0.3, which corresponds to a difference of 6 points in the USE (assuming a standard deviation of 20)) with a Type I error of 0.05 and a power of 80%, a total sample size of 280 patients (140 per group) is needed for statistical analysis. Taking into account a dropout rate of about 40% (patients who give informed consent but do not return the questionnaire by post), 480 patients shall be recruited. In the intention-to-treat analysis, the larger number of patients is expected to be compensated by a dilution of effects, meaning that the power will be approximately the same as in the available case analysis.

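### The primary t test leaves out the factors that stratify randomisation (physician, disease, migration background), a modest and avoidable loss of efficiency

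*Protocol article*

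**What the plan says.** Under Administration, the protocol article has envelope contents centrally randomised, "stratified by physician, disease and migration background (Turkey, Poland, Russia, Italy) with varying block sizes". Each physician holds separate sets of envelopes by disease and migration background.

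Under Statistical analyses, the primary outcome "will be analyzed by a blinded statistician with a one-sided *t* test". That test is described only as "comparing the scores on the USE scale between the intervention and the control group". No stratification factor is part of that comparison. The rest of the section does not add one:

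- ANCOVA is reserved for secondary outcomes that have a baseline measurement.
- Disease and migration background appear only as subgroups, among the additional analyses.
- The one named covariate, acculturation, also belongs to the additional analyses and is not a stratification factor.
- Linear mixed models are named for handling missing data, with no physician or stratum term.

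Under Sample size, the trial is sized "with a Type I error of 0.05 and a power of 80" per cent for an effect that "corresponds to a difference of 6 points in the USE". The calculation is made "assuming a standard deviation of 20". This leads to the statement that "a total sample size of 280 patients (140 per group) is needed for statistical analysis". Recruitment is then raised to 480: "Taking into account a dropout rate of about 40" per cent.

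**The concern.** Stratified blocks remove between-stratum variation from the treatment contrast to the extent that they balance the arms. A two-sample t test still counts that variation as noise. If the strata predict USE, the test's standard error is then larger than the true one and some of the precision from stratifying is not used. Where blocks stay unfilled, chance imbalance between language groups or diseases goes uncorrected.

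It is plausible that the strata matter. Patients read and answer in one of four languages, the brochures differ by disease, and the Methods/Design section says both conditions are expected to be sensitive to cultural background. At stake are a few points of power and, in a well-balanced trial, a one-sided error rate somewhat under 5%.

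**Working it through.** **Inputs from the article:** difference 6 points, SD 20, type I error 0.05, power 80%, 280 analysed (140 per group), 480 recruited, about 40% non-return, one-sided t test. **Assumption:** the share of USE variance explained by the strata, R², is not given; 5%, 10% and 15% are used.

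**1. Reproduce the plan's figure.** Per group, n = 2 × ((1.645 + 0.842) × 20 / 6)² = 137.4, rounded up to 138, or 276 in total against 280 stated. At 140 per group, SE = 20 × √(2/140) = 2.39 and power = Φ(6/2.39 − 1.645) = 80.7%. The two-sided version would need 350. So the trial was sized for the unadjusted one-sided test with the full SD.

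**2. Patients analysed.** 480 × 0.60 = 288, or 144 per arm. Nominal SE = 20 × √(2/144) = 2.357, and 6/2.357 = 2.546.

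**3. Both tests under full balance within strata.** The true SE is 2.357 × √(1 − R²), but the t test still uses 2.357.

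- Unadjusted power = Φ((2.546 − 1.645)/√(1 − R²))
- Adjusted power = Φ(2.546/√(1 − R²) − 1.645)
- Actual one-sided error of the t test = 1 − Φ(1.645/√(1 − R²))

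| R² | Unadjusted power | Adjusted power | Gap (points) | t test error |
|---|---|---|---|---|
| 0.05 | 82.2% | 83.3% | 1.1 | 4.6% |
| 0.10 | 82.9% | 85.0% | 2.1 | 4.1% |
| 0.15 | 83.6% | 86.8% | 3.2 | 3.7% |

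At R² = 0 the two tests have the same power and the error is 5%.

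**4. Sparse strata and non-return.** Each physician has 2 × 4 = 8 cells, and non-return breaks up the blocks. The number of physicians is not stated, so it was assumed.

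- *Error rate.* With 480 recruited, 60% returned, blocks of 2 or 4 and 20, 40 or 80 physicians, the t test's one-sided error was 4.4% to 5.1% for R² of 0.05 to 0.15 (8,000 runs per setting, Monte Carlo SE about 0.24 points).
- *Power.* In smaller simulations (280 analysed, 600 runs per setting), the model with fixed disease and background and a random physician intercept was compared with the t test. At R² = 0.10, power was 84.7% against 81.3% with 40 physicians and 83.2% against 80.3% with 20. At R² = 0.05 it was 84.0% against 83.3% and 80.7% against 79.0%. These gaps of about 1 to 3 points agree with step 3 within simulation error.

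**5. How physician is modelled.** With 40 physicians as fixed effects, adjustment lost power at R² = 0 (73.5% against 80.5%) and at R² = 0.10 (79.2% against 81.4%). It gained only at larger values (83.9% against 82.7% at R² = 0.20).

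**The case against.** The strongest reply is that nothing planned fails. Randomisation keeps the unadjusted difference unbiased, the test does not exceed its error rate, and the sample size was calculated for this test and reproduces. The variance share is an assumption and could be close to zero. Mixed models are already named, and a full analysis plan may give them stratum terms. With recruitment under way, changing the primary test needs a documented amendment.

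Most of this stands and limits the point to efficiency. It does not remove it: the article itself fixes the primary test as unadjusted, and the mixed models it names are for missing data.

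Three stronger readings are tempting, and the document does not support them:

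- *The standard error is too wide and the error rate is below 5%.* This holds only so far as balance within strata survives. Full balance gives 3.7% to 4.6%; small cells and non-return bring the error back close to nominal.
- *Adjustment lifts power from about 81.6% to between 83% and 87%.* The 81.6% is Φ(2.546 − 1.645), which credits the t test with no benefit from balance, while a conservative error rate presumes full balance. The two cannot be combined. Under full balance the unadjusted test itself reaches 82.2% to 83.6%.
- *The sample size or the test is invalid.* Neither is.

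**Conclusion.** The point holds as a modest loss of efficiency. Design and primary analysis do not match: three factors stratify the allocation and none enters the primary test. Adjustment is worth about 1 to 3 points of power at 144 per arm if the strata explain 5% to 15% of USE variance, and nothing if they explain none. The t test is mildly conservative at most.

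The direction is certain if the strata predict USE. The size rests on the assumed variance share, on an assumed number of physicians for the sparse-strata results, and on analysing returned questionnaires; the intention-to-treat analysis with imputation was not modelled. The change is worth making because it needs no new data and has little downside, not because the planned analysis would mislead.

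**What to change.** Before unblinding, pre-specify the primary test as the one-sided arm contrast in USE at T1 from a linear mixed model with fixed effects for disease and migration background and a random intercept for physician. Do not fit a separate fixed effect for each physician, since that can cost power. Keep the unadjusted t test as a supporting analysis.

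The cost is a documented, dated amendment to the analysis text. Recruitment was still open when the article was submitted, and the statistician for the primary analysis is blinded, so the change can be made credibly. No data collection is added: the physician and the envelope set identify all three factors for every randomised patient. The sample size need not change.

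### The primary t test on all randomised patients needs filled-in USE scores for about 40% of them; if these come from single EM imputation, either the 5% error rate is lost or the effect is shrunk by about 40%

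*Protocol article*

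**What the plan says.** Under Statistical analyses, the protocol article states that the primary outcome "will be analyzed by a blinded statistician with a one-sided" t test comparing USE scores between the two groups. It continues: "The primary analysis will be performed according to the intention-to-treat principle, including all randomized participants". The next sentence is "Missing data will be handled by applying linear mixed models and expectation-maximisation imputation". Secondary analyses, by contrast, use available cases.

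Under Sample size, the target is a difference of 0.3 SD, "which corresponds to a difference of 6 points in the USE (assuming a standard deviation of 20"). The error rate and power behind the calculation are given as "with a Type I error of 0.05 and a power of 80"%. From this the article concludes that "a total sample size of 280 patients (140 per group) is needed for statistical analysis". It then allows for "a dropout rate of about 40% (patients who give informed consent but do not return the questionnaire by post") and plans to recruit 480.

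The same section adds that the intention-to-treat analysis has more patients than the available-case analysis, but that the effect will be diluted, so that power comes out about equal.

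**The concern.** The USE score at T1 comes only from the postal questionnaire. With 40% of 480 not returned, about 192 primary scores will not exist. A t test needs one score per patient. Of the two named methods, only EM imputation supplies scores; a mixed model estimates the arm contrast directly and leaves nothing for a t test to do. If the mixed model is the intended primary analysis, the stated t test is not. The text therefore allows two different primary p-values.

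The reading closest to the words is an EM-filled data set followed by a t test. In its usual form EM imputation writes one value per missing score, and the t test treats it as observed. Filled-in scores add nominal sample size without adding information. Limiting EM to single missing items in returned questionnaires would be nearly harmless, but the t test could then not include all randomised patients, and the remark about a larger intention-to-treat sample would have no basis. At stake are the error rate and the effect estimate of the trial's primary comparison.

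**Working it through.** **Inputs from the article.** One-sided test, alpha 0.05, power 80%, difference 6, SD 20, 140 per group evaluable, 480 recruited, about 40% not returned.

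**Assumptions not in the article.** Equal allocation (240 per arm); scores missing at random (in the simulation, completely at random and equally often in both arms); single imputation; imputation predictors explaining a share R² of 0 to 0.5 of the variance in USE. Low R² is plausible: in Table 1 every self-rating starts at T1, so a T1 non-returner offers only GP data, the stratification factors and any T2 or T3 return.

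**Reproducing the plan's figures.** n per arm = 2(1.645 + 0.842)²/0.3² = 137.4, so 138; the t-test correction gives 139. The stated 140 agrees, with power 80.5%. Recruitment: 280/0.6 = 467, and 480 is close. Expected returns are 0.6 × 480 = 288, or 144 per arm; missing scores are 192. An available-case t test at 144 per arm has power of about 81%.

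**Case A: arm in the imputation model, conditional means filled in, R² = 0.**
- True SE = 20√(2/144) = 2.36, because only 144 per arm carry information.
- SD seen by the t test = 20√0.6 = 15.5; its SE = 15.5√(2/240) = 1.41.
- Ratio = 1.41/2.36 = 0.60.
- One-sided type I error = P(Z > 1.645 × 0.60) = P(Z > 0.987) = 16.2%.
- At 30% missing the same formula gives 12.5%, and at 50% it gives 20.5%.

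**Case B: arm left out, pooled mean filled in, R² = 0.**
- Expected difference = 0.6 × 6 = 3.6.
- Under the null the t test's SE (1.41) matches the true SE of this estimator (1.41), so the 5% level holds.
- Power: the SE under a 6-point effect is about 1.42; 3.6/1.42 = 2.54; P(Z > 1.645 − 2.54) = about 81%.
- If residual noise is added so that the SD stays near 20, SE = 20√(2/240) = 1.83; 3.6/1.83 = 1.97; power = P(Z > 1.645 − 1.97) = about 63%.

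**Simulation** (20,000 runs under the null, 5,000 under a 6-point effect):

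| Imputation model | R² | Type I error, means filled in | Type I error, noise added | Mean estimate of a true 6 (means filled in) | Power, means filled in | Power, noise added |
|---|---|---|---|---|---|---|
| With arm | 0 | 16.7% | 13.3% | 6.0 | not meaningful | not meaningful |
| With arm | 0.5 | 10.3% | 9.6% | 6.0 | not meaningful | not meaningful |
| Without arm | 0 | 4.6% | 4.8% | 3.6 | 81% | 62% |
| Without arm | 0.5 | 5.0% | 4.9% | 3.6 | 71% | 62% |

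Power with arm is not meaningful because the 5% level is not held.

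**Against the article's own reasoning.** The Sample size section expects a diluted effect with unchanged power. Case B with constant filled-in scores produces that pattern: 3.6 points and 81%. Power survives there only because identical filled-in values shrink the SD from 20 to about 15.5. Restore the SD and power is about 62%. Neither a mixed model nor multiple imputation by arm would dilute the effect when scores are missing at random.

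**The case against.** The strongest reply is that the article never says the imputation is single, never says whether arm is in the imputation model, and names linear mixed models first. USE is measured at T1, T2 and T3, so a mixed model with a T1 contrast is available and needs no filled-in scores. Single imputation is therefore an inference, and that part of the reply stands.

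A reader might go further and infer that the plan's false-positive rate is inflated outright. The documents do not support that. Inflation arises only with arm in the imputation model, and the dilution remark points to the other case, where the level is held and the error is conservative. The 16% is also the upper end, for predictors that explain nothing.

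It can also be said that imputation details belong in an analysis plan that is not shown. That would be fair if the article were silent. It instead fixes a test, a population and two missing-data methods that do not fit together, and builds its power argument on the result.

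Finally, dilution might be meant as a real feature, since some non-returners will not have read the brochure. That is an assumption about how non-returners differ from returners. It would need to be stated as such, and EM imputation under missing at random does not supply it.

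**Conclusion.** The point holds in conditional form. As written, the primary t test on all randomised patients needs filled-in scores for about 192 of 480, and the article does not fix which of its two methods yields the primary p-value. If single EM imputation is used, no version gives both a valid test and an unbiased estimate. With arm in the model, the SE is about 0.60 of its true value at R² = 0, and one-sided type I error is about 10-16% over R² from 0.5 to 0. With arm left out, the 5% level is kept but a 6-point difference appears as about 3.6, and power near 80% depends on an artificially reduced SD. These sizes rest on 240 per arm, 40% missing at random, SD 20 and single imputation. A definite claim that the 5% level is broken would go beyond the text.

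**What to change.** Name one primary analysis in Statistical analyses, before unblinding. Either of these will do:
- a likelihood-based linear mixed model of USE at T1, T2 and T3 with arm, visit, arm-by-visit and the stratification factors, with the arm contrast at T1 as the primary one-sided test;
- multiple imputation by arm, combined with Rubin's rules.

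State that single EM imputation will not be used for unreturned questionnaires. State also that patients who return no questionnaire add no USE information under either option, because USE has no measurement before randomisation. Remove the dilution remark in Sample size, or reconcile it with the chosen analysis. The 280 evaluable and 480 recruited can stand. A delta-shift sensitivity analysis for non-returners is optional; it would address return depending on how useful the brochure was.

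The cost is analysis wording only, with no new patients or data. The nominal SE will be larger than with EM-filled scores: about 2.36 rather than 1.41 points if predictors add nothing.
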